# Clinical effectiveness of hypertonic sodium lactate infusion for intraoperative brain relaxation in patients undergoing scheduled craniotomy for supratentorial brain tumor resection: A study protocol of a single center double-blind randomized controlled phase II pilot trial

**DOI:** 10.1097/MD.0000000000031038

**Published:** 2022-10-07

**Keywords:** anesthesia, brain relaxation, craniotomy, intracranial pressure, mannitol, neurosurgery, sodium lactate

## Abstract

**Methods and analysis::**

We designed a phase II randomized, controlled, double-blind, single-center pilot trial, and aim to include 50 adult patients scheduled for craniotomy for supratentorial brain tumor resection under general anesthesia. Patients will be randomized to receive either mannitol (conventional group) or hypertonic sodium lactate (intervention group) infusion at the time of skin incision. Brain relaxation (primary outcome) will be assessed immediately after opening the dura by the neurosurgeon blinded to the treatment allocated using a validated 4-point scale. The primary outcome is the proportion of satisfactory brain relaxation, defined as brain relaxation score of 3 or 4.

**Ethics and dissemination::**

This study was approved by the Ethics Committee (Comité de Protection des Personnes Est III) and authorized by the French Health Authority (Agence Nationale de Sécurité des Médicaments, Saint-Denis, France). The University Hospital of Besancon is the trial sponsor and the holder of all data and publication rights. Results of the study will be submitted for publication in a peer-review international medical journal and for presentation in abstract (oral or poster) in international peer-reviewed congresses.

**Registration::**

The trial is registered with ClinicalTrials.gov (Identifier: NCT04488874, principal investigator: [name], date of registration: July 28, 2020).

Key PointsThis is the first study to investigate the clinical effectiveness of molar sodium lactate infusion for intraoperative brain relaxation in patients scheduled for craniotomy.Brain relaxation is assessed using a validated 4-point scale by the neurosurgeon in charge of the patient blinded to the treatment allocated.Single-center double-blind randomized phase II pilot trial.The study is not designed to compare the 2 groups with adequate statistical power but will provide high-quality data to design further studies.

## 1. Introduction

The management of cerebral edema and intracranial pressure (ICP) is a critical component of intraoperative care of patients undergoing brain surgery.^[1,2]^ Tumor size and peritumoral brain edema increase ICP and satisfactory brain relaxation is crucial to improve surgical conditions in patients undergoing craniotomy for supratentorial brain tumor resection.^[1]^ Surgical retractors used to access the surgical site locally increase the pressure exerted on the underlying parenchyma and can contribute to retraction ischemia reperfusion injuries and vasogenic edema in healthy brain areas.^[3,4]^

Hyperosmolar solutions are widely prescribed in neurosurgery patients to decrease ICP and to improve brain relaxation prior to surgical incision.^[1]^ The hyperosmolarity combined to impermeability of the blood–brain barrier to osmotically active substances favor the move of water from the brain to the intravascular compartment.^[1]^ Mannitol is traditionally considered the standard and the first-choice solution for brain relaxation in neurosurgery patients.^[1]^ The mannitol effect is mainly related to an osmotic mechanism leading to brain dehydration and brain relaxation. Moreover, mannitol could increase cerebrospinal fluid absorption and cerebral perfusion pressure leading to vasoconstriction and decreased cerebral blood volume.^[5–7]^ The dose of 1.0 g/kg of 20% mannitol infused at the time of skin incision appeared to have the best benefits risks ratio in patients undergoing craniotomy for supratentorial brain tumor.^[8]^ However, it provides satisfactory brain relaxation in only 65% of patients and side effects such as dehydration, hypotension, renal failure, and rebound effect after transitory action was reported.^[8–10]^

Molar sodium lactate was proposed as an alternative to 20% mannitol in severe brain-injured patients.^[11,12]^ Two randomized trials reported that hypertonic sodium lactate infusion might be more efficient than 20% mannitol to prevent and treat ICP episodes after traumatic brain injury.^[11,12]^ The reduction in ICP provided by hypertonic sodium lactate could stay longer since lactate catabolism triggers a shift of chloride anion from the intracellular to the extracellular compartment to maintain plasma electroneutrality.^[13]^ The shift of chloride anion could lead to a reduction in brain volume resulting from the movement of water from the brain to the intravascular comportment that persists several hours after the end of lactate sodium infusion without any rebound effect.^[14]^ Moreover, sodium lactate infusion might contribute to increase intracerebral concentration of lactate that could prevent the impaired cerebral energetics related to brain ischemia reperfusion injuries.^[15–19]^ To date, the clinical effectiveness and safety of hypertonic sodium lactate infusion for brain relaxation in patients undergoing scheduled craniotomy for supratentorial brain tumor resection have never been investigated.

## 2. Objectives

The study was designed to describe the clinical effectiveness of hypertonic sodium lactate infusion on intraoperative brain relaxation in patients undergoing scheduled craniotomy for supratentorial brain tumor resection.

## 3. Methods and Analysis

This study is written in accordance with the SPIRIT guidelines for the reporting of interventional trial protocols.^[20]^

### 3.1. Trial design

This study is a phase II prospective randomized, controlled, double-blind, single center pilot trial.

### 3.2. Eligibility

Adult patients scheduled for craniotomy for supratentorial brain tumor resection under general anesthesia in the Ne University Hospital of Besancon, France (Centre Hospitalier Universitaire (CHU) de Besancon) are eligible for inclusion. Inclusion and exclusion criteria for the present study are listed below.

### 3.3. Inclusion criteria

Signed informed consent.American Society of Anesthesiologists’ (ASA) physical status I to III.Scheduled craniotomy for supratentorial brain tumor resection under general anesthesia requiring brain relaxation.Unilateral brain tumor.Ability to speak, write, and understand French language.Patient affiliated to French Social Security or equivalent.

### 3.4. Exclusion criteria

ASA physical status IV or higher.Emergent surgery.Age under 18 years or over 75 years.Preoperative Glasgow Coma Scale < 13.Body mass index < 18 kg/m^2^ or > 30 kg/m^2^.Body weight > 100 kg.Hyponatremia < 130 mmol/L or hypernatremia > 145 mmol/L.Hypokalemia < 3.5 mmol/L.Preoperative osmotherapy (mannitol, hypertonic saline, or hypertonic sodium lactate) within 24 h prior surgery.Congestive heart failure.Estimated glomerular filtration rate (MDRD formula) < 60 ml/min/1.73 m^2^.Moderate to severe liver dysfunction with a Child Pugh ≥ B7.Myasthenia.Extra ventricular drainage or ventriculoperitoneal shunt.Diagnosed dementia.Contraindication to propofol, remifentanil, atracurium, or cisatracurium administration.Allergy to mannitol or any of its excipients.Allergy to hypertonic sodium lactate or any of its excipients.Legal incapacity or limited legal capacity.Subjects without health insurance.Pregnant of breast-feeding women.Subjects within the exclusion period of another study.

### 3.5. Study outline

Eligible patients are screened and informed during the anesthesia consultation. Written informed consent is obtained the day before surgery by investigators after oral explanation of the study. After written informed consent is obtained, patients are randomized using a computer-generated randomization list implemented on the CleanWeb web-based system (Telemedicine Technologies, France).

After randomization, a first cognitive assessment using a battery of validated neuropsychological tests (see below) is performed by an investigator who was specifically trained by a neuropsychologist (GC) prior to the start of the study. Patient characteristics, past medical history including ASA physical status, type of brain tumor, preoperative management of brain tumor (corticosteroid therapy, antiepileptic therapy, chemotherapy, and/or radiotherapy), preoperative Karnosky performance status, and preoperative neurological status including Glasgow Coma Scale are collected. Midline shift, brain tumor size, and localization, and the size of peritumoral edema are extracted from the preoperative brain imaging [either brain magnetic resonance imaging (MRI) or computed tomography scan]. Included patients undergo a first cognitive assessment using a battery of validated neuropsychological tests (see below).

On arrival in the operating room, standard monitoring (General Electric Healthcare) is put in place. A peripheral venous catheter dedicated to anesthetic drug infusion is inserted in a forearm vein. All patients receive intravenous anesthesia based on manually driven target-controlled infusion of propofol and remifentanil aiming to maintain bispectral index (BIS) values between 40 and 60. All patients are paralyzed using nondepolarizing neuromuscular blocking agent (either cisatracurium or atracurium).

After induction of anesthesia, patients are intubated, and tidal volume and respiratory rate are set to maintain the end-tidal carbon dioxide between 35 and 40 mm Hg. Inspired oxygen fraction is adjusted to obtain a pulse oximetry ≥ 95%. A second peripheral venous catheter, a urinary catheter, and an indwelling arterial catheter introduced in a radial artery are implemented.

The treatment allocated by randomization for brain relaxation, that is, mannitol (conventional group) or hypertonic sodium lactate (intervention group) infusion, is started at the time of skin incision and is administered over 15 to 20 minutes (see below). The degree of brain relaxation (primary outcome) is assessed by the neurosurgeon immediately after opening the dura. If a greater degree of brain relaxation is required, a rescue therapy is administered according to the following stepwise strategy: (1) administration of additional mannitol 0.25 g/kg; (2) deepening anesthesia to achieve a BIS value between 20 and 40; and (3) administration of an intravenous bolus of sodium thiopental 5 mg/kg.

Blood samples are collected immediately before skin incision (baseline, T_0_), and at 30 minutes, 60 minutes, 180 minutes, 24 hours, and 48 hours after the end of osmotherapy (either mannitol or hypertonic sodium lactate) to measure blood pH, natremia, kaliemia, lactatemia, and serum osmolality. Serum levels of S100B protein and neuron-specific enolase (NSE) are measured at baseline, and at 24 hours and 48 hours after the end of osmotherapy.

The following surgical and anesthetic details are recorded: type and duration of surgery; intraoperative blood loss and urine output, blood transfusion and total volume of fluids infused; type and total dose of drugs administered; and all blood pressure, heart rate, pulse oximetry, and end-tidal carbon dioxide values from induction of anesthesia to discharge from the operating room.

At the end of surgery, patients are admitted to the postoperative surgical intensive care unit during at least the first postoperative 24 hours. Postoperative neurological status (Glasgow Coma Scale, new transient, or permanent neurological deficits), urine output, blood transfusion, and total volume of fluids infused are assessed on days 1 and 2 after surgery. Brain MRI is performed within the first 2 days after surgery to quantify postoperative brain edema and ischemic changes, and postoperative midline shift.

Karnosky performance status, postoperative morbidity (cardiac arrythmia within 2 days after surgery, length of stay in the intensive care unit and in the hospital, surgical wound infection, pneumonia, readmission in the intensive care unit or in the hospital, surgical revision for postoperative intracerebral hematoma and/or life-threatening intracranial hypertension, coma, seizure, stroke, any permanent neurological deficit, any drug-related adverse event), and postoperative mortality are assessed on day 30 after surgery.

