### 3.6. Randomization, allocation concealment, and blinding

Randomization is performed the day before surgery using the CleanWeb web-based system (Telemedicine Technologies, France). A computer-generated permuted-block randomization list with varying block sizes (ratio 1:1) was implemented on the website at the beginning of the study by an independent data manager. The block size is unknown to the investigators. When written informed consent was obtained, the investigator entered data online regarding each patient to enable inclusion and randomization. The treatment randomly allocated to the patient is immediately provided to the investigator by the website.

Patients and outcome assessors (neurosurgeons) are blinded to the treatment allocated.

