### 3.8. Outcome measures

The primary outcome is the proportion of satisfactory brain relaxation, defined as brain relaxation score of 3 or 4. Brain relaxation is assessed immediately after opening the dura by the neurosurgeon in charge of the patient blinded to the treatment allocated. The assessment of brain relaxation is performed using a validated 4-point scale,^[21]^ with: 1 = bulging brain; 2 = firm brain; 3 = satisfactorily relaxed; and 4 = perfectly relaxed).

Secondary outcomes are proportion of patients requiring a rescue therapy to improve the degree of brain relaxation during surgery; blood pH, serum osmolality, natremia, kaliemia, and lactatemia at baseline (before skin incision), and at 30 minutes, 60 minutes, 180 minutes, 24 hours, and 48 hours after the end of osmotherapy (either mannitol or hypertonic sodium lactate); serum levels of S100B and NSE proteins at baseline and at 24 hours and 48 hours after the end of osmotherapy; postoperative recovery assessed by the Glasgow Coma Scale on day 1 and on day 2 after surgery and by the Karnofsky performance status on day 30 after surgery; cognitive performance at baseline (the day before surgery) and on day 2 after surgery; volume of postoperative brain edema assessed on brain MRI performed on day 2 after surgery; and postoperative morbidity and mortality on day 30 after surgery.

Cognitive performance is assessed the day before surgery and on day 2 after surgery using a battery of validated neuropsychological tests during a 20-min face-to-face interview with an investigator who was specifically trained by a neuropsychologist (GC) prior the start of the study. Seven neuropsychological tests are performed to explore 5 different cognitive domains: (a) attention, using the Trail Making Test, part A; (b) executive function, using the Trail Making Test, part B and the semantic-phonemic switching verbal fluency test; (c) verbal fluency, using the Isaacs Set Test and the semantic-phonemic clustering verbal fluency test; (d) learning and episodic verbal memory, using the Memory Impairment Screen test; and (e) verbal short term and working memory, using the forward and reverse digit span memory test.

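### The baseline cognitive battery follows randomization, and nothing in the article keeps the allocation from the investigator who gives it, so this secondary outcome is open to rater bias

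*Protocol article*

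**What the plan says.** Four statements in the protocol article bear on this point.

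- **Order.** Section 3.5 first has "After written informed consent is obtained, patients are randomized using a computer-generated randomization list", and then "After randomization, a first cognitive assessment using a battery of validated neuropsychological tests (see below) is performed by an investigator". Section 3.6 fixes the day: "Randomization is performed the day before surgery using the CleanWeb web-based system".
- **Who learns the arm.** Section 3.6: "The treatment randomly allocated to the patient is immediately provided to the investigator by the website". What is released is the treatment itself.
- **Who is blinded.** Section 3.6: "Patients and outcome assessors (neurosurgeons) are blinded to the treatment allocated". Section 3.1 labels the whole trial double-blind.
- **What is measured, and by whom.** Section 3.8 lists as a secondary outcome "cognitive performance at baseline (the day before surgery) and on day 2 after surgery". A specially trained investigator gives seven tests in a face-to-face interview of about 20 minutes at each visit.

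Section 3.12 plans comparisons of the two groups by intention to treat at a significance level of 0.05.

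**The concern.** A baseline value is normally safe from allocation bias because it is recorded before anyone can know the arm. Here that protection is given up without need. The battery comes after randomization, and by then the arm has been disclosed to someone with the same job title as the person who gives the tests.

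These tests are given and scored by a rater. Instruction, prompting, timing and scoring can all vary with what the rater expects. If the rater knows the arm, a baseline difference between groups could come from the rater and not from chance. On day 2 the rater's knowledge could act on the outcome itself. A reader of the results would take the double-blind label to cover cognition, and the article does not secure that.

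**Working it through.** The plan gives no figure on this point, so the main check is to read the sections together.

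1. **Is the order explicit?** Yes. Section 3.5 gives consent, randomization, then the first cognitive assessment. The same section mentions the first assessment a second time without placing it relative to randomization, which does not change the order. Section 3.8 places the baseline on the day before surgery, the same day as randomization in section 3.6. Either order would therefore fit within that day.
2. **Is the arm known to someone at that moment?** Yes. Section 3.6 has it provided immediately to the investigator who enters the patient.
3. **Is that person the cognitive rater?** Not stated. Section 3.5 says an investigator trained by a neuropsychologist; section 3.6 says the investigator. They may be the same person or different people.
4. **Is the rater covered by the blinding statement?** Not by its wording. The parenthesis after outcome assessors narrows the term to neurosurgeons, who score brain relaxation. The cognitive rater is an investigator and is not named.
5. **Does the day-2 test differ?** No. It is also given by an investigator, with no blinding stated.
6. **Is the primary outcome exposed?** No. Section 3.8 has it scored by a neurosurgeon blinded to treatment.

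**Illustration only.** The documents give no estimate of any rater effect, of its direction, or of the correlation between visits. Section 3.8 defines no change score. To show the scale, assume:

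- 25 patients per arm (section 3.11), a two-sided 0.05 test and no true effect;
- baseline scores shifted by b SD in one arm only, with day-2 scores unshifted;
- a baseline to day-2 correlation r of 0.5 to 0.7.

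For a change score, SE = √(2(1−r)) × √(2/25), and the standardized shift is d = b/SE. At r = 0.5, SE = 1 × 0.283 = 0.283, so b = 0.2 gives d = 0.71. With adjustment for baseline, d = r·b / (√(1−r²) × √(2/25)). The false-positive rate in both cases is P(|Z + d| > 1.96).

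| Assumed shift b | Change score, r = 0.5 to 0.7 | Baseline-adjusted, r = 0.5 to 0.7 |
|---|---|---|
| 0.1 SD | 6.4% to 7.4% | 5.5% to 6.4% |
| 0.2 SD | 10.9% to 15.0% | 6.9% to 10.7% |
| 0.3 SD | 18.6% to 27.8% | 9.4% to 18.0% |

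A small shift barely moves the error rate; a larger one would matter. An equal shift at both visits would cancel in a change score. Nothing in the documents says which row applies, if any.

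**The case against.** The strongest reply is that the key link is inferred. No section says that the rater is the person who receives the allocation, or that the arm is passed on. Staff separation and website access rights are details that an article may leave to the full protocol. This stands as far as it goes: a reader might infer that the cognitive raters are unblinded, and the article does not say so. Silence about the rater is not a statement that the rater knows the arm. But the order of the steps is stated, not left out, and no analysis plan can turn a measurement taken after randomization into one taken before it.

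Several further replies also stand, and they limit the point:

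- The patient is blinded, and no study infusion is given until skin incision the next day. Treatment cannot affect the baseline; only rater behaviour can.
- The tests are described as validated and the rater as trained, which leaves less room for bias.
- Cognition is one of many secondary outcomes. The objective in section 2 is descriptive, and the Key Points say that the study is not powered to compare the groups.

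A reader might also infer that all seven tests are biased, or that a particular false-positive rate follows. The documents support neither. They show that the outcome is exposed, not that it is distorted.

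**Conclusion.** The point holds in a limited form. As written, the protocol takes the cognitive baseline after randomization, releases the arm to an investigator, and contains no step that keeps it from the investigator who tests cognition at baseline and on day 2. This secondary outcome can therefore be biased by rater knowledge of the arm.

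The conclusion about order rests on explicit text. The conclusion about exposure rests on the absence of any stated safeguard and on reading the blinded assessors as neurosurgeons, as the text itself does. The size of any bias is unknown. The effect on the primary outcome and on the sample size is nil. This is a modest weakness, worth correcting because most of it can be removed at almost no cost.

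**What to change.** - **Section 3.5:** complete the baseline cognitive battery after consent and before randomization in CleanWeb. Both steps already fall on the day before surgery, so this swaps two steps and can use the same staff. It fully protects the baseline.
- **Section 3.6:** where existing staffing allows, have the day-2 battery given by a trained investigator who has not received the allocation, and add that role to the blinded parties. This may need a second trained person; the article does not describe staffing, so the cost cannot be judged from it. Where it is not possible, report the cognitive outcome as not assessor-blinded.
- **Patients already enrolled:** inclusions began on September 29, 2020, so reordering protects only later patients. For the others, record which order was used and whether the rater knew the allocation at each visit, and report this with the cognitive results.

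None of this changes the sample size, the primary outcome or the planned tests.

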Postoperative morbidity includes cardiac arrythmia that occurs within 2 days after surgery, any complication requiring surgical revision, unexpected cerebral edema, intracranial hypertension, intracerebral hematoma, stroke, seizure, coma, readmission in the intensive care unit or in the hospital, surgical wound infection, or pneumonia.

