### 3.10. Safety

All serious adverse events are collected and reviewed by the principal investigator and reported to the trial sponsor (CHU Besancon, Besancon, France), to the Pharmacovigilance Department of our institution and to the independent Data Safety and Monitoring Board (DSMB). Study insurance has been contracted for all participants by the trial sponsor (CHU Besancon, Besancon, France).

Since off-labeled use of hypertonic sodium lactate is prescribed in patients included in the interventional group. All serious adverse events will be reviewed and analyzed by the independent DSMB after the inclusion of the first 25 patients to decide whether the study should be stopped prematurely for safety reasons.

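### One item of the day-30 morbidity list depends on an unprotected causality judgement, and the two morbidity lists disagree on whether it belongs

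*Protocol article*

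**What the plan says.** Section 3.5 of the Protocol article gives a day-30 list of "postoperative morbidity (cardiac arrythmia within 2 days after surgery, length of stay in the intensive care unit and in the hospital, surgical wound infection, pneumonia" and further named complications. It closes with "any permanent neurological deficit, any drug-related adverse event), and postoperative mortality are assessed on day 30 after surgery". Only the item "any drug-related adverse event" carries a causality condition.

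Section 3.8 defines the same secondary outcome again: "Postoperative morbidity includes cardiac arrythmia that occurs within 2 days after surgery, any complication requiring surgical revision, unexpected cerebral edema", followed by more named events. It has no drug-related item.

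Section 3.10 deals with serious events and applies no causality filter: "All serious adverse events are collected and reviewed by the principal investigator and reported to the trial sponsor". An independent board reviews them after the first 25 patients.

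On blinding, 3.6 says: "The treatment randomly allocated to the patient is immediately provided to the investigator by the website". It then names patients and the neurosurgeons, as outcome assessors, as blinded. The Introduction says that the "clinical effectiveness and safety of hypertonic sodium lactate infusion for brain relaxation" in this surgical setting have not been studied, and 3.10 describes the use as off-label.

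**The concern.** A randomized comparison of harms is fair when events are counted by the same rule in both arms. A rule that admits an event only if someone thinks a drug caused it depends on what that person believes about the drug. Here the article itself gives unequal prior expectations. The Introduction lists side effects for mannitol, presents lactate as free of rebound, and says that lactate's safety in this setting is unstudied. Someone who knows the arm could over-attribute events to the unfamiliar drug or wave through familiar mannitol effects, so the bias could go either way.

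The word drug is also left open. Every patient receives several anesthetic agents, and the rescue steps can add mannitol in either arm.

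At stake is the count of the remaining non-serious harms in a pilot whose stated purpose is to supply good data for later trials.

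**Working it through.** **1. Which harms reach the analysis without attribution**

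| Type of harm | Where recorded | Causality judgement needed? |
|---|---|---|
| Serious adverse events | 3.10 | No |
| Arrhythmia, wound infection, pneumonia, seizure, stroke, coma, readmission | 3.5 and 3.8 | No |
| Mortality to day 30 | 3.5, 3.8 | No |
| pH, sodium, potassium, lactate, osmolality at six time points | 3.5, 3.8, 3.9 | No |
| Intraoperative blood pressure, heart rate, oximetry, end-tidal CO2 | 3.5 | No |
| Neurological deficits, urine output, fluids, transfusion on days 1 and 2 | 3.5 | No |
| Other non-serious events | 3.5, last item of the morbidity list | **Yes** |

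The last row is what remains. An infusion-site reaction falls there. So would non-serious renal impairment: the Introduction names renal failure as a mannitol side effect, but it is in neither list and no renal marker is among the laboratory measures stated.

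**2. The two morbidity lists**

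The list in 3.5 has length of stay, any permanent neurological deficit and the drug-related item; the list in 3.8 has none of these. The list in 3.8 has unexpected cerebral edema and any complication requiring surgical revision. The list in 3.5 does not have the edema item and restricts revision to hematoma or life-threatening intracranial hypertension. They cannot both define the outcome.

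**3. The plan's own figure**

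Section 3.11 gives 25 per arm for an accuracy of 20 points. With n = 1.96² × p(1 − p) / 0.20²:
- p = 0.55 gives 23.8, so 24.
- p = 0.50 gives 24.01, so 25.

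The figure reproduces and is not in dispute. It sets the denominators below.

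**4. How few decisions matter**

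Section 3.12 fixes the level at 0.05, taken here as two-sided, and Fisher's exact test is one of its two options for qualitative variables. With equal arms, the two-sided p is twice the one-sided tail:
- 0 v 5: 2 × C(25,5)/C(50,5) = 2 × 53,130/2,118,760 = 0.0502
- 0 v 6: 2 × C(25,6)/C(50,6) = 2 × 177,100/15,890,700 = 0.0223
- 1 v 6: 2 × [C(25,7) + 25 × C(25,6)]/C(50,7) = 2 × 4,908,200/99,884,400 = 0.098
- 1 v 7: 2 × [C(25,8) + 25 × C(25,7)]/C(50,8) = 2 × 13,099,075/536,878,650 = 0.0488

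One relatedness call moves the item from 0.098 to 0.049, or from 0.050 to 0.022.

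**5. Illustration under assumed rates**

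The documents give neither event rates nor attribution rates, so all rates here are assumptions. The counted rate is the true patient-level rate times the probability of being judged related. The table gives the probability of p ≤ 0.05 (Fisher, 25 per arm) when the true rates are equal in both arms.

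| Attribution, mannitol v lactate | True rate 20% | 40% | 60% |
|---|---|---|---|
| All events counted | 0.02 | 0.03 | 0.03 |
| 30% v 60% | 0.02 | 0.11 | 0.19 |
| 20% v 80% | 0.11 | 0.45 | 0.72 |

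In the other direction, take true rates of 20% (mannitol) v 60% (lactate). Counting all events detects the difference with probability 0.79. With attribution of 90% v 30%, both counted rates become 18% (0.20 × 0.90 and 0.60 × 0.30) and the probability is 0.02.

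**The case against.** A reader might infer three stronger things from the text, and none is supported.

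- *That non-serious harms in general enter only through this item.* Arrhythmia, seizure, wound infection and pneumonia can be non-serious and are counted whatever their cause. The biochemical effects most to be expected from either infusion are measured in every patient.
- *That an unblinded investigator makes the judgement.* Section 3.6 shows only that the investigator who randomizes learns the arm. The article does not name the person who judges relatedness or say what that person knows. What can be said is that no protection is stated.
- *That the trial's safety comparison could be created or erased by attribution.* Most of it does not pass through attribution, serious events have independent review, and the Key Points disclaim adequate power to compare the groups.

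Two further objections carry weight. The article condenses a full protocol that is not shown, and adverse-event recording and causality procedures are commonly left there. The illustration also rests on invented rates, and with mild differential attribution or rare events it shows almost no effect (0.02 at a true rate of 20% and attribution of 30% v 60%).

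What survives is a criticism of a stated rule, not of a silence: the article writes a causality condition into one morbidity item, and its second list contradicts the first. The disclaimer on power does not remove this, because attribution distorts the event rate itself as well as the test.

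**Conclusion.** The point holds in a narrow form and is of low severity. One item of the day-30 list is open to attribution that differs by arm, and it is unclear whether that item belongs to the secondary outcome at all. The conflict between 3.5 and 3.8 can be read directly from the text. The sensitivity to a few decisions follows from 25 per arm, assuming all are analysed and the item is compared with a two-sided Fisher test. The size of any bias cannot be derived from the documents; under the assumed rates it runs from negligible to large. If the full protocol already records all adverse events regardless of cause, only the wording in 3.5 and its mismatch with 3.8 remain.

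**What to change.** 1. Use one morbidity list in 3.5 and 3.8, and state whether length of stay, permanent neurological deficit, unexpected cerebral edema and the adverse-event item are part of the outcome.
2. Replace the drug-related item by: *any adverse event from the start of the allocated infusion to day 30, whatever its presumed cause*, with infusion-site events included explicitly.
3. Tabulate it by arm with exact confidence intervals. Keep the causality opinion as a descriptive column, and do not use it to decide what is counted.

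The cost is modest: more entries for 50 patients who are already assessed on days 1, 2 and 30, and more background postoperative events in both arms. It is not purely a wording change, because inclusions began in September 2020 (4.2). Patients followed before the change should be identified in the analysis, or their records reviewed under the new wording, so that ascertainment is the same throughout.
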